### Registration and Research Consent

Eligible participants will complete a structured registration and consent process prior to engaging with the e-coaching platform. A Qualtrics survey will be administered to collect demographic data (eg, age, gender), secure informed consent, and capture email addresses necessary for platform registration. After completing the survey, participants will be registered on the e-coaching platform using the provided email addresses, receiving a one-time login password along with detailed access instructions. Participation in tests, surveys, and interviews will not affect the quality of care they receive from the community. This study does not involve drug usage or medical treatment, and there are no anticipated physical or medical risks to participants.

### Randomization

Randomization will be conducted using random permuted blocks of three through an online computer randomization system. Participants will be randomly assigned to one of three groups: (1) the full intervention group, where participants will receive the complete e-coaching with full content (ie, 6 sessions); (2) the need-specific intervention group, where participants will receive tailored e-coaching sessions extracted from the full module (ranging from 2 to 6 sessions) based on individual needs; or (3) the control group, where participants will receive video-based educational information about caregiving for 6 weeks.

To maintain allocation concealment, the randomization sequence will be generated prior to participant recruitment and will be securely stored by the research team leader. This approach ensures that those enrolling participants cannot foresee group assignments, thereby minimizing selection bias. In terms of implementation, the intervention will be delivered through an e-platform accessible to participants. This platform will facilitate the distribution of content and support participant engagement throughout the study period. Outcome assessors will be blinded to group assignments to minimize the potential bias in outcome measurement. Participants will be informed that they may not know which group they are assigned to, and they will be encouraged to focus on their personal experiences with the content provided.

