## Methods

### Study Design

This study is a 3-arm, single-blinded randomized controlled trial developed in accordance with the SPIRIT (Standard Protocol Items: Recommendations for Interventional Trials) checklist (Table 1). The research team will perform individual randomization using statistical software and assign the content through an e-platform to carers with mild needs. It will consist of a 6-week intervention period, with a screening process to be conducted prior to the intervention implementation. Statistical comparisons will be performed at baseline (T0), immediately postintervention (T1), and at a 3-month follow-up (T2) (Table 1). This study will be conducted from April 2025 to September 2026.

**Table 1. T1:** Schedule of enrollment, intervention, and assessments.

	Study period					
	Enrollment	Allocation	Postallocation			
Timepoint	*−t* _1_	0	Baseline	Treatment	Immediately postintervention	3 months postintervention
Enrollment						
Initial eligibility screen	✓					
Informed consent	✓					
Allocation		✓				
Interventions						
e-coaching 1				✓		
e-coaching 2				✓		
Control				✓		
Assessments						
JCCSP^a^ carer multidimensional need assessment	✓		✓		✓	✓
PHQ-9^b^			✓		✓	✓
GAD-7^c^			✓		✓	✓
EQ-5D-5L			✓		✓	✓
WHOQOL-BREF^d^			✓		✓	✓
ZBI-12^e^			✓		✓	✓
SCSES-10^f^			✓		✓	✓
CD-RISC-10^g^			✓		✓	✓

a JCCSP: Jockey Club Carer Space Project.

b PHQ-9: 9-Item Patient Health Questionnaire.

c GAD-7: 7-Item General Anxiety Disorder Questionnaire.

d WHOQOL-BREF: World Health Organization Quality of Life–BREF.

e ZBI-12: Zarit Burden Interview.

f SCSES-10: 10-Item Self-Care Self-Efficacy Scale.

g CD-RISC-10: 10-Item Conner-Davidson Resilience Scale.

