### Sample Size Estimation

Sample size was calculated using analysis of covariance adjusting for baseline, and the longitudinal linear mixed model will be used as the primary analysis to use all repeated measures and available data.

According to a prior meta-analysis, internet-based self-help interventions for mental health demonstrate a medium effect size when compared to passive control conditions such as care-as-usual and waitlist [49]. According to another systematic review and meta-analysis of the effectiveness of internet-based psychoeducation programs for carers of people with dementia, internet-based psychoeducation programs had a significant impact on reducing carers’ depressive symptoms, with an effect size of −0.19 compared to control conditions [50].

Power analysis was conducted with G*Power 3.1.9.7. Assuming a medium effect size in the analysis of covariance, *α*=.05, power=0.80 [51], a total of 158 participants are required to join the study. Considering a possible attrition rate of 33%, the research team will set the minimum sample size at 240, with 80 participants in each arm [52].

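### A fixed block of three for three equal arms means the stated safeguards do not support the guarantee that assignments cannot be foreseen

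*Protocol article*

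**What the plan says.** Study Design: "This study is a 3-arm, single-blinded randomized controlled trial". Sample Size Estimation sets the total and the split: "the research team will set the minimum sample size at 240", "with 80 participants in each arm". The allocation ratio is therefore 1:1:1.

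Randomization gives the method, "random permuted blocks of three through an online computer randomization system", and a single block size. On concealment it says that "the randomization sequence will be generated prior to participant recruitment and will be securely stored by the research team leader", and concludes: "This approach ensures that those enrolling participants cannot foresee group assignments, thereby minimizing selection bias". No other reason is given for that conclusion.

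On who does what, Study Design says "The research team will perform individual randomization using statistical software", and that the same team assigns the content on the platform. Randomization states that outcome assessors are blinded and that participants are told they may not know their group. It does not say whether those who enrol are kept from past allocations. Participant Recruitment describes rolling entry, expected to take 12 months, from 10 support units and 8 shared venues run by 6 partners. Table 1 places eligibility screening and consent before allocation, but puts the baseline assessment under the postallocation columns. The Results section reports that enrolment is ongoing and expected to close in May 2026.

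**The concern.** When the block size equals the number of arms, every block is a permutation of the three arms, and its last place follows from the first two. Locking the list away does not change this, because the deduction uses allocations already made and not the list. The safeguard offered and the guarantee drawn from it therefore do not connect.

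What is at stake is selection at entry. If someone involved in enrolment can tell which arm comes next, the timing of a carer's entry can be influenced, and rolling recruitment leaves room for that. The primary outcomes, GAD-7 and PHQ-9, are self-reported. Analysis can adjust for measured imbalance, but not for unmeasured traits such as motivation. Sample size and power are not affected.

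**Working it through.** **Inputs.** Three arms (Study Design); 240 participants, 80 per arm (Sample Size Estimation); block size 3 (Randomization). The article gives no figure for predictability, so there is none to reproduce.

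**The plan's own total.** Taking its medium effect as f = 0.25 (an assumption, since the value is not printed), an analysis of covariance with three groups and one covariate, α = 0.05 and power 0.80 needs 158 participants, as stated. Allowing for 33% attrition gives 158/(1 − 0.33) = 235.8, so 236. The stated 240 is slightly higher and makes 240/3 = 80 complete blocks.

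**The observer.** The figures below are for someone who knows the block size, where each block starts, and every earlier allocation in it. They are ceilings.

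1. A block of three has 3! = 6 equally likely orders.
2. The best guess is right with probability 1/3 at the first place, 1/2 at the second and 1 at the third.
3. Certain allocations: one per block, so 80 × 1 = 80 of 240 (33.3%).
4. Correct guesses: (1/3 + 1/2 + 1)/3 = 61.1%, against 33.3% under simple randomization.
5. If only control versus either e-coaching arm matters, more is fixed, because once control has appeared the rest of the block must be e-coaching. Per block this is (1/3) × 2 + (2/3) × 1 = 4/3 allocations, that is 4/9 = 44.4%, or about 107 of 240.

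**Other fixed block sizes, same observer.** The larger sizes are illustrative.

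| Fixed block size | Certain | Of 240 | Correct guesses |
|---|---|---|---|
| 3 | 33.3% | 80 | 61.1% |
| 6 | 20.0% | 48 | 56.1% |
| 9 | 14.3% | about 34 | 53.2% |

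With sizes that vary at random and are not disclosed, the observer also loses the block boundaries on which these figures depend.

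**A recruiter with a partial view.** The article states no stratification by site, so one sequence appears to run across 10 + 8 = 18 recruitment points. Assume, for illustration, that entry is equal and independent across points.

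- Both earlier allocations in a block come from the recruiter's own point with probability (1/18)² = 0.3%, or 80 × 0.003 = about 0.2 of the 80 determined allocations.
- If everyone in one of the 6 partner organisations shares what they know, the probability is (1/6)² = 2.8%, or about 2 of the 80.

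The recruiter would still need to know where the block starts.

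**The case against.** The strongest reply is that predictability on paper is not foresight in practice. Foresight needs the block boundary and both earlier allocations, and the article nowhere says that those enrolling have either. Carers enter at many points, may complete the screening form alone, and receive their content individually through the platform. Eligibility rests largely on stated criteria and a scored assessment, and Table 1 already puts screening and consent before allocation. Who can see past allocations is the kind of operational detail that a condensed article may leave to the full protocol. All of this stands, and it is why 61% and 80 of 240 are ceilings.

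It is also fair that block size alone is not the remedy: fixed blocks of 6 or 9 still give the same observer 56% and 53%. Keeping past allocations from those who enrol matters at least as much.

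Three stronger readings are tempting and are not supported:

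- A reader might infer that concealment has failed. No text shows that anyone has foreseen an allocation.
- A reader might infer that past allocations are visible within the research team, because that team both randomizes and assigns content. The article does not say so; it only leaves the possibility open.
- A reader might see a contradiction between the statistical software in Study Design and the online system in Randomization. The two are compatible: an online system is software, or one may generate the list and the other release it.

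What the reply does not answer is the guarantee itself. The point does not rest on an omitted detail. The block size, the safeguard and the conclusion are all printed, and the conclusion does not follow from the safeguard.

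**Conclusion.** The point holds in a limited form. A fixed block of three is the most predictable permuted block available for three equal arms, and its size has been published while enrolment is open. For an observer with full knowledge of boundaries and past allocations, at most 80 of 240 assignments are certain and at most 61% of guesses are right, against 33% by chance. For a recruiter at a single venue, the exposure under equal independent entry is a fraction of one allocation. Secure storage of the list does not address either case, and the article does not say that those enrolling are kept from past allocations. The claim that the approach *ensures* assignments cannot be foreseen is therefore not supported by the safeguards stated. That is a statement about what has been assured, not evidence that selection bias has occurred.

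**What to change.** For the allocations that remain:

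- Regenerate the unused part of the list, starting at a block boundary, with randomly varying block sizes in multiples of three. Do not disclose the sizes while enrolment is open.
- Keep past allocations from those who enrol, and say so.
- Release each allocation only after eligibility, consent and the baseline assessment are complete, and move baseline ahead of allocation in Table 1.

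For participants already allocated under blocks of three, reword the guarantee. For example: the list was stored securely by the team leader; blocks were of fixed size three; foresight by a person who knew the earlier allocations in a block cannot be excluded by these measures alone. If the full protocol records who had access to past allocations, cite that.

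The cost is small: the list has to be regenerated, and arm sizes may differ by a few participants. With a largest block of nine, for example, an unfinished final block can leave two arms at most 9/3 = 3 apart. If enrolment has already closed, only the rewording applies.

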### Outcome Measures

The same set of outcome measures will be assessed in 3 groups and across different time points. An intention-to-treat principle will be used for data analysis, in which all participants will be assessed with the same set of outcome measures across 3 measurements, regardless of adherence to their assigned intervention. Several measures will be used to capture the between-group treatment effects, including the PHQ-9 and the GAD-7 as the primary outcomes. The 22-Item Carer Multidimensional Need Assessment, EQ5D5L, World Health Organization Quality of Life–BREF (WHOQOL-BREF), Cantonese short version of Zarit Burden Interview (CZBI-Short-12), 10-Item Self-Care Self-Efficacy Scale (SCSES-10), and 10-Item Connor-Davidson Resilience Scale (CD-RISC-10) will be captured as secondary outcomes. The survey will primarily be self-administered using Qualtrics, and we estimate that it will take approximately 1 hour for participants to complete. However, if participants are unable to finish the questionnaire on their own, we will facilitate their completion of the survey via face-to-face interviews at their choice of venue or via telephone or online interviews depending on their preference.

### Intervention

#### e-Coaching Intervention (1 and 2)

The experimental group receives an e-coaching intervention based on LiCBT, lifestyle intervention, and interpersonal effectiveness. This program is designed to operate on an e-platform individually in an interactive, story-based, and self-directed format. It consists of 6 weekly sessions, each lasting about 10 to 30 minutes. Intervention group adherence will be the number of assigned modules completed by the participants. In between each session, participants are assigned home practices to further reinforce the skills learned. e-Coaching 1 will include all content listed in Table 2. e-Coaching 2 will include content tailored to the specific needs of carers, which will be identified using the 22-Item Carer Multidimensional Need Assessment, covering 5 domains of needs, including physical health, mental health, social support, caregiving needs, and caregiving ability (Table 3). This approach ensures that each participant in e-coaching 2 receives more focused material that directly addresses their specific needs.

**Table 2. T2:** Session plan of e-coaching intervention group.

Session	Content and activity	Home practice
Carer online self-directed platform	Introduction of the relationship between online self-directed content and the situation of carer Mindfulness practice	Nil
Lifestyle intervention	Healthy lifestyle Mindfulness practice (standing) Mindfulness practice (stretch)	Mindfulness practice Healthy lifestyle planning
Sleep	Myths about sleep Sleep cycles and hygiene Mindfulness and breathing relaxation practice	Mindfulness practice Breathing relaxation practice Sleep hygiene
Family relationships and communication	Unspoken rules in families Communication skills in the family Mindfulness practice	Mindfulness practice Identify unspoken rules in families Improving communication patterns with family members
Emotion regulation	Identify different emotions Understand emotion mechanism Regulate negative emotion	Mindfulness practice Accumulate positive emotions
Respite time for carers	What is respite service, and why does it matter? Planning respite Mindfulness practice	Mindfulness practice Planning respite time
Caregiving skills for the older adults	Educational content on information, resources, and skills of caregiving for older adults	Nil

**Table 3. T3:** Domains of carer’ needs and e-Coaching modules assigned.

Needs or modules	Introduction	Emotion regulation	Caregiving skills	Sleep	Respite time for carers	Lifestyle intervention	Family relationships and communication
Mental health	✓	✓	✓	✓			
Physical health	✓			✓		✓	
Caregiving ability	✓	✓	✓		✓		
Social support	✓				✓		✓
Caregiving needs	✓	✓	✓				

#### Control Group

On the other hand, the placebo-controlled group attends 6 weekly online sessions that primarily provide video-based educational information in a self-directed format on the same e-platform. The focus of the content will be on practical caregiving skills and promoting general well-being, rather than targeting any particular psychological or mental health–related factors directly. The control group will include all content listed in Table 4. The total duration of the control group lasts about 50 minutes. Control group adherence will be the number of videos completed by the participants. The control condition is designed as an “information-only” educational comparator, reflecting standard educational resources typically accessible to caregivers in the community. It does not include the interactive e-coaching component or structured home practice and does not overlap with the content provided in the intervention arm. This approach allows us to test the intervention materials and evaluate the added value of interactive e-coaching and guided self-help practice over standard educational materials.

**Table 4. T4:** Topics and content of control Group.

Topics	Content
Caregiving experience	Video regarding sharing of other carers’ experiences.
Introduction to knowledge of aging-related health issue and pain management	Videos of early detection of dementia and emotional problems. Videos address strategies for managing and alleviating chronic pain in older adults.
Caregiving resources	Videos of community support resources, including hotline, respite, equipment rental services, useful mobile apps, and support network of community centers.

### Outcome Measures

#### Primary Outcomes

##### 7-Item Generalized Anxiety Disorder

The GAD-7 is a widely used screening tool that measures the severity of generalized anxiety disorder by assessing the frequency of anxiety symptoms experienced over the past 2 weeks. Respondents rate their experiences on a 4-point scale from “not at all” to “nearly every day,” providing a reliable assessment of anxiety severity [53].

##### 9-Item Patient Health Questionnaire

The PHQ-9 is a self-report instrument used to assess depression symptoms, consisting of 9 items that correspond to the diagnostic criteria for major depressive disorder. Participants will rate the frequency of symptoms experienced over the past 2 weeks, helping to determine the severity of depressive symptoms [54]. The last item serves as a screening question for suicide risk, requiring further assessment if answered affirmatively.

### Secondary Outcomes

#### 22-Item Carer Multidimensional Need Assessment

The 22-Item Carer Multidimensional Need Assessment was developed based on a large-scale population survey on carers’ well-being in Hong Kong. This tool covers six need domains: (1) carers’ health challenges, (2) carers’ mental ill health, (3) lack of support, (4) high care challenges, (5) caregiving capacity, and (6) risk or need for immediate support.

#### EQ-5D-5L

The EQ-5D-5L is a standardized instrument for measuring general health status. It consists of 5 dimensions: mobility, self-care, usual activities, pain or discomfort, and anxiety or depression. For each dimension, respondents choose from 5 levels ranging from “no problems” to “extreme problems.” The EQ-5D-5L is a widely used, preference-based measure of health-related quality of life. It is designed for self-completion by respondents and is applicable to a wide range of health conditions and treatments [55].

#### The World Health Organization Quality of Life–BREF

The WHOQOL-BREF is a 28-item instrument developed by the World Health Organization to assess an individual’s quality of life across 4 domains: physical health, psychological health, social relationships, and environment. Each item is scored on a 5-point Likert scale, with higher scores indicating a better quality of life. The WHOQOL-BREF provides a concise yet comprehensive evaluation of an individual’s overall well-being, making it a widely used tool in research, clinical practice, and public health assessments. Policy 21 Hong Kong Limited has been commissioned by the Hong Kong Jockey Club Charities Trust to conduct a survey on the quality of life of the target service users in the Jockey Club’s elderly and elderly services. The survey results will help the Jockey Club to plan and formulate projects [56,57].

#### 12-Item Cantonese Short Version of the Zarit Burden Interview

The CZBI-Short-12 is a brief questionnaire used to measure carer burden in individuals caring for a family member with a chronic illness or disability. It has been validated in Hong Kong and a spoken Cantonese version of the 12-Item ZBI to assess the burden on carers in clinical and community settings. Each item subjectively measures caregiver burden on a 5-point Likert scale, with possible answers ranging from 0 (never) to 4 (very frequently) [58].

#### Self-Care Self-Efficacy Scale

The SCSES-10 is a measurement tool used to assess an individual’s self-efficacy. Self-care self-efficacy for chronic illness has been tested in the Hong Kong population. This 10-item instrument measures self-efficacy related to self-care maintenance, monitoring, and management in patients with chronic illness. Each item is rated on a 5-point Likert scale, ranging from 1 (not at all confident) to 5 (totally confident). A higher score represents a higher level of self-efficacy [59].

#### 10-Item Connor-Davidson Resilience Scale

The CD-RISC-10 is a 10-item, self-administered scale that assesses an individual’s level of resilience. Each item is rated on a 5-point Likert scale, ranging from 0 (not true at all) to 4 (true all of the time). The total possible scores range from 0 to 40, with higher scores being an indicator of high resilience [60,61].

### Statistical Analysis

#### Primary Outcome Analysis

The linear mixed model will be used to evaluate the hypothesis regarding whether there is a reduction in anxiety and depression symptoms in the intervention groups compared to the control group. The model will include treatment conditions (e-coaching 1, e-coaching 2, and Control), assessment time points (baseline, immediately post intervention, and 3 months post intervention), and their interaction (group-by-time) effects as fixed effects. To account for the correlation of repeated measures within individuals, a random intercept for participants will be included. Anxiety and depression scores will serve as the dependent variables in separate models. Statistical significance is defined as alpha levels less than .05. Planned contrasts will separately compare each active intervention group (e-coaching 1 and e-coaching 2) against the control group at immediately post intervention and 3-month follow-up to evaluate intervention efficacy. Holm-Bonferroni correction will be applied to control the familywise error rate across multiple contrasts.

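### The primary mixed model does not adjust for the baseline score and fixes equal correlation between visits, so the T1 and T2 contrasts lose precision that could be had almost free

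*Protocol article*

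**What the plan says.** Primary Outcome Analysis fits separate linear mixed models to the anxiety and depression scores. The fixed effects are treatment condition, "assessment time points (baseline, immediately post intervention, and 3 months post intervention), and their interaction (group-by-time) effects as fixed effects". For within-person correlation, "a random intercept for participants will be included"; no other covariance structure is named. Each active arm is then compared with control at T1 and at T2, with Holm-Bonferroni correction.

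Sample Size Estimation states: "Sample size was calculated using analysis of covariance adjusting for baseline, and the longitudinal linear mixed model will be used as the primary analysis". It goes on: "Assuming a medium effect size in the analysis of covariance", with "power=0.80 [51], a total of 158 participants are required to join the study". Then: "Considering a possible attrition rate of 33%, the research team will set the minimum sample size at 240", which is 80 per arm.

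No baseline covariate and no common baseline mean is named. The Sensitivity Analysis section adds demographics such as sex and age, not the baseline score. Secondary Outcomes Analysis uses the same fixed effects for the continuous scales and says that full information maximum likelihood will use all available data.

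**The concern.** When arm, time and their interaction are all free, the model estimates a separate baseline mean for each arm and makes no use of the fact that randomisation equates those means in expectation. A contrast at T1 or T2 then has two possible meanings:

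- **Visit contrast:** the difference between arms at that visit. With complete data this is the raw difference in means, and chance baseline imbalance stays in it.
- **Change contrast:** the group-by-time term, which is a difference in change from baseline.

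Neither is the baseline-adjusted comparison, and the section does not say which is intended. At stake is precision on both primary outcomes.

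Separately, a random intercept with ordinary residuals implies one variance and one correlation for all pairs of visits. T0 to T1 spans the 6-week intervention; T0 to T2 adds 3 months. If correlation falls with time, the model-based standard errors of the change contrasts are wrong, in opposite directions at T1 and T2.

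**Working it through.** **Reproducing the plan's figure.** Inputs from Sample Size Estimation: alpha .05, power 0.80, three arms, medium effect. No number is given for the effect; f = 0.25 is assumed as the conventional value. Noncentral F test with 2 numerator df, λ = N·f², df2 = N − 3 − 1. At N = 158, λ = 158 × 0.0625 = 9.875 and power is 0.802, so 158 reproduces. It stays 158 with 0, 1, 2 or 3 covariates, so it credits no baseline correlation. Attrition: 158/0.67 = 236, rounded up in the plan to 240.

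**Precision.** Inputs: N = 80 baselines per arm (plan) and n = 53 completers per arm (158/3, rounded; 80 × 0.67 = 53.6). The baseline–follow-up correlation r is not in the documents; 0.6 is assumed, with 0.5 to 0.7 as the range. Also assumed: equal variances (SD = 1), dropouts contribute baseline only, data missing at random, r treated as known. The likelihood uses the baselines of dropouts, so the variances per arm are:

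- Baseline-adjusted: (1 − r²)/n
- Visit: (1 − r²)/n + r²/N
- Change: (1 − r²)/n + (1 − r)²/N

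At r = 0.6:

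- Adjusted: 0.64/53 = 0.01208
- Visit: 0.01208 + 0.36/80 = 0.01658; ratio 1.373; SE ratio 1.17; equivalent sample loss 1 − 1/1.373 = 27%
- Change: 0.01208 + 0.16/80 = 0.01408; ratio 1.166; SE ratio 1.08; equivalent sample loss 14%

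| Assumed r | SE penalty, visit | SE penalty, change |
|---|---|---|
| 0.5 | 10% | 10% |
| 0.6 | 17% | 8% |
| 0.7 | 28% | 6% |

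**Power.** Inputs: d = 0.5 on the raw SD (assumed), two-sided alpha .05/4 = .0125 (first Holm step, taking the four contrasts for one outcome as the family), r = 0.6, noncentral t with 104 df. The SE of the contrast is √(2 × variance per arm).

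| Contrast | SE | d/SE | Power |
|---|---|---|---|
| Baseline-adjusted | 0.155 | 3.22 | 75% |
| Change | 0.168 | 2.98 | 67% |
| Visit | 0.182 | 2.75 | 58% |

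**Equal-correlation structure.** Complete data and equal variances; assumed correlations 0.7 (T0–T1), 0.5 (T0–T2) and 0.6 (T1–T2). The random-intercept model uses their mean, 0.6, so both change contrasts get relative variance 2(1 − 0.6) = 0.80.

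- T1: true value 2(1 − 0.7) = 0.60; SE ratio √(0.80/0.60) = 1.155; size of a nominal 5% test 2[1 − Φ(1.96 × 1.155)] = 2.4%
- T2: true value 2(1 − 0.5) = 1.00; SE ratio √(0.80/1.00) = 0.894; size 2[1 − Φ(1.96 × 0.894)] = 8.0%

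With 0.6, 0.4 and 0.6 instead, the sizes are 3.4% and 8.4%. In both cases the visit contrast keeps 5%, because the variances are equal.

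**The case against.** **The sizing difference is disclosed.** One sentence names analysis of covariance for the sizing and the mixed model for the analysis. A reader might infer that the trial was sized on a precision its analysis cannot deliver, and that 158 is therefore wrong. The documents do not support this: 158 is the same with or without a covariate, and nothing says that the medium effect was meant on the baseline-adjusted scale. This objection stands.

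**Complete-case arithmetic overstates the loss.** Counting only 53 completers per arm gives SE penalties at r = 0.6 of 1/√(1 − 0.36) = 1.25 (visit) and √(2/1.6) = 1.12 (change). A reader might quote 25% and 12%. The plan expects attrition and uses all available data, so the smaller figures above apply. This also stands.

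**The two worst results belong to different readings.** The larger precision loss is for the visit contrast; the inflated T2 error is for the change contrast. They cannot both be charged to the plan. The hypotheses speak of a greater reduction in scores, which leans towards change, where the penalty is about 8%.

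**The remedy has its own assumption.** Table 1 puts the baseline assessment after allocation. If participants knew their arm or had content before completing it, equal baseline means could not be taken for granted. This limits the fix.

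**An analysis plan could add detail.** It could, for example on residual structure. But the protocol positively states the fixed effects and the random intercept, and a plan that followed them would carry them forward.

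**Conclusion.** The point holds as a worthwhile, low-cost improvement, not as an error in the sample size or a source of bias: with complete data, randomisation keeps either contrast unbiased. The model as stated leaves the contrast undefined between two versions, both less precise than a baseline-adjusted one. The cost in standard error is about 17% (visit; 10% to 28% for r from 0.5 to 0.7) or about 8% (change; 10% to 6% over the same range). These figures rest on assumed correlations, 80 baselines and 53 completers per arm, and missingness at random.

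The distortion of type I error is conditional. It needs the change reading and correlation that falls with time. A reader might take the 8% as the error rate of the primary analysis in general; the documents give no correlations to support that, and with equal variances the visit contrast is unaffected.

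**What to change.** 1. Define the four contrasts per outcome as baseline-adjusted differences between each active arm and control at T1 and at T2.
2. Obtain them from a model with a common baseline mean across arms and arm effects only at T1 and T2, or from a model with T1 and T2 as outcomes and baseline score-by-time as covariate.
3. Replace the random intercept by an unstructured 3×3 within-person covariance, fitted by REML with Kenward-Roger degrees of freedom.
4. Use the same model for the continuous secondary outcomes.
5. Confirm that baseline is completed before assignment is revealed or content is released. If it is not, do not assume the common baseline mean without first checking baseline completion by arm.

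The cost is a few sentences in the analysis plan and four extra covariance parameters (six in place of two). No extra data or participants are needed, and the change can be made before the analysis, which the protocol expects to complete by September 2026.
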